## Abstract

**Background:**

Although insufficient sleep has emerged as a strong, independent risk factor for obesity in children, the mechanisms by which insufficient sleep leads to weight gain are uncertain. Observational research suggests that being tired influences what children eat more than how active they are, but only experimental research can determine causality. Few experimental studies have been undertaken to determine how reductions in sleep duration might affect indices of energy balance in children including food choice, appetite regulation, and sedentary time. The primary aim of this study is to objectively determine whether mild sleep deprivation increases energy intake in the absence of hunger.

**Methods:**

The Daily, Rest, Eating, and Activity Monitoring (DREAM) study is a randomized controlled trial investigating how mild sleep deprivation influences eating behaviour and activity patterns in children using a counterbalanced, cross-over design. One hundred and ten children aged 8–12 years, with normal reported sleep duration of 8–11 h per night will undergo 2 weeks of sleep manipulation; seven nights of sleep restriction by going to bed 1 hr later than usual, and seven nights of sleep extension going to bed 1 hr earlier than usual, separated by a washout week. During each experimental week, 24-h movement behaviours (sleep, physical activity, sedentary behaviour) will be measured via actigraphy; dietary intake and context of eating by multiple 24-h recalls and wearable camera images; and eating behaviours via objective and subjective methods. At the end of each experimental week a feeding experiment will determine energy intake from eating in the absence of hunger. Differences between sleep conditions will be determined to estimate the effects of reducing sleep duration by 1–2 h per night.

**Discussion:**

Determining how insufficient sleep predisposes children to weight gain should provide much-needed information for improving interventions for the effective prevention of obesity, thereby decreasing long-term morbidity and healthcare burden.

**Trial registration:**

Australian New Zealand Clinical Trials Registry ACTRN12618001671257. Registered 10 October 2018.

## Background

Childhood obesity is a major issue worldwide, and New Zealand (NZ) is no exception; one in three children are overweight or obese with marked ethnic and socioeconomic inequities present [1]. Given established difficulties in treating childhood obesity [2, 3], early prevention is considered key [4]. However, changing diet and physical activity behaviours long-term has proven difficult among children as well as adults [2, 3], highlighting the need to examine alternative approaches to effective weight management. Interest is growing in the potential for sleep as a novel component of weight management [5, 6], given the extensive observational literature demonstrating short sleep duration as a strong, independent risk factor for obesity in children [7–10], and promising experimental evidence indicating that sleep interventions can substantially reduce the risk of obesity in early childhood [11–13]. However, it is currently not clear how insufficient sleep leads to weight gain [5, 14, 15], as the majority of research has been cross-sectional or cohort in nature limiting the ability to infer causality.

### How sleep affects energy intake

Observational literature suggests that not getting enough sleep influences what children eat, with shorter sleep duration associated with poorer quality diets [5, 16–19]. For example, using objective sleep measures, observational research has shown that sleep duration is negatively associated with energy density of the diet [5], independent of potential confounders such as screen time, physical activity, parental education level and ethnicity of the parents, suggesting that inadequate sleep is an independent risk factor for making poor nutritional choices in children [20]. Another study combined objective and subjective measures to report a one hour decrease in sleep duration over a 200 day period to be associated with higher intake of sugary beverages in children [17]. While most studies have measured dietary indices, very few studies actually measure energy intake; this is probably because the assessment of energy intake generally requires the use of diet recalls or food diary records, which pose a greater respondent and researcher burden. Of the limited research to date, one study showed short sleep duration to be associated with higher energy intake in infants [21], whereas no relationship was found in children [22].

Few experimental studies have manipulated sleep to determine the effects of measures of energy balance during growth, particularly in younger children. To date, only two trials have attempted to determine how dietary intake changes when sleep is experimentally restricted in children aged 12 and under, and these have both demonstrated that when sleep duration is reduced, energy intake increases [23, 24]. In these studies, reducing sleep by 2–3 h per night for up to five nights increased energy intake by 7–21%, a substantial amount on a daily basis, especially over time [23, 24]. However, these studies did not examine why energy intake differed - whether through a change in food choices, or because eating frequency or food quantity consumed increased. The reasons why sleep affects changes in energy intake in children need to be investigated in order to hone effective interventions.

### How sleep affects eating habits and behaviours

Sleep manipulation studies in children have tended to focus on adverse cognitive outcomes [25], but greater attention is now being paid to other aspects of sleep health [26], such as the association between decreased sleep duration and unhealthy lifestyle factors including dietary habits and activity levels [9, 10, 27]. A preference for energy-dense foods, irregular eating habits, and more external and emotional eating are all factors implicated in obesity [5, 16–19]. Despite huge international interest in sleep, experimental studies examining how being tired affects what, when and how school-aged children eat, are not common. Do children choose different foods? Does their appetite change? Do caregivers change what types of food they offer their tired, and possibly behaviourally challenging, child? These questions remain unanswered in experimental research, partly because of difficulties in measuring these important behaviours of importance, and partly because of the variety and quality of sleep measures used in studies, making quantification of studies in the field, and therefore providing causal statements about sleep and diet, problematic. Anecdotally, caregivers report that they parent differently when their child is tired, by being more conciliatory or by using treat foods as rewards. It has been established that when children are rewarded with food, this practice is associated with greater food intake [28]; however, no studies have systematically determined whether child-rearing behaviours around food and activity change when a child is sleep deprived.

Generally, relatively little is known about the context of eating, including what children might be doing at the same time (for example, socializing, watching television, or using screens) [29, 30]. However, some observational research suggests that a high degree of ‘food responsiveness’ (eating in response to factors other than hunger) at least partly mediates the relationship between sleep and weight in children [31]. Experimental studies in older children indicate that sleep deprivation was associated with choosing foods characterized by higher glycaemic index and glycaemic load with a trend toward more calories and carbohydrates [32, 33].

Although the measurement of the context of eating has previously been difficult [34], the advent of wearable technology, such as lapel cameras, offers a unique opportunity to examine what influences eating behaviour in children in a remarkably unobtrusive yet objective manner [35, 36]. Furthermore, given the well-established difficulties inherent in dietary assessment, wearable technology used in tandem with diet recall can enhance the accuracy of dietary reporting [37]. Applied here, such wearable technology could provide valuable complementary information to improve understanding of the effects of sleep deprivation on food intake itself, as well as context behind food intake, among children. For example, although screen time is known to increase dietary intake relative to non-screen behaviours in children, quantifying this effect has been difficult using questionnaires [38], and using camera images might allow for the quantification of the number of eating occasions per day where screens are present. Consumption of snacks, particularly less nutrient dense sweet and savoury snacks is already high in children during the evening hours [39]. Our research team has previously found that more than half of all meals captured on film during the evening were consumed whilst adolescents watched screens [40]. Additionally, social facilitation (a phenomenon when people eat more when they are in a bigger group), while evident in adults, requires more research in children [41, 42]. Using wearable cameras would allow for the examination of these questions passively in children, rather than in an artificial laboratory situation which may change behaviour.

### How sleep affects physical activity and sedentary time

Several studies of physical activity and sleep in children have shown a negative relationship between sleep duration and physical activity among children [9]. Shorter sleep duration has been associated with increased sedentary time, as the fatigue caused by short sleep increases lethargy and affects general mood [5, 43–45], and shorter sleep latency has been demonstrated in those children who participate in more physical activity during the day [46]. It makes sense to consider that sleep deprivation and the consequence of being tired might impact on physical activity in children; however, there is little experimental evidence that short sleep impacts on any component of energy expenditure, including physical activity [9, 47]. Methodological limitations may play a part in this [48]. As time spent asleep and time spent physically active both sit within a 24 h window, they are co-dependent so that if children sleep less, they have to do more of something else within those 24 h – e.g. spend more time in sedentary activities such as screen use, and/or more time being active. Whether or not reductions in sleep time are offset by increases in sedentary time or physical activity (measured via actigraphy, and compared by baseline versus intervention) is something that has not yet been investigated in children [49]. Only appropriate compositional analyses that account for the closed nature of the 24 h window and the co-dependence of these activities can determine the true effect of substituting one activity for another [48, 50]. National physical activity guidelines have recently promoted the importance of measuring all activity behaviours across the full 24-h day, that is, sleep, sedentary time, and physical activity [51, 52]. As such, collecting, analysing, and interpreting 24-h movement data becomes more important, but is complicated and requires appropriate statistical techniques that account for this compositional data [48].

Together, these findings suggest viable links between sleep and diet, but experimental studies are required to determine causality. The Daily Rest, Eating and Activity Monitoring (DREAM) study will assess the effect of mild sleep deprivation on eating behaviour in children aged 8–12 years, using both objective and subjective measurements. Use of a cross-over design reduces confounders, as each participant receives the same number of experimental manipulations over the same amount of time. Using technology in tandem with 24-h diet recalls will provide unique information on the environmental context of eating under different sleep conditions. By using well-established methods combined with novel approaches to improve understanding of how not getting enough sleep adversely affects health in children, we can potentially take the next steps in offering new pathways for decreasing the risk of obesity.

### Aims and objectives

The primary aim of the DREAM study is to determine whether mild sleep deprivation increases energy intake in the absence of hunger (measured objectively). Secondary aims will determine whether mild sleep deprivation: 1) influences the amount and types of foods eaten, 2) alters the context of eating (e.g. where, when, who with, what else is happening), 3) changes other indices of eating behaviour (e.g. emotional over-eating), 4) changes children’s preference for different food types, 5) changes how caregivers care for their child with regards to snacking and meals, and 6) influences time spent in sedentary or physical activity.

We hypothesize that, when compared to being well-rested, children whose sleep is restricted by one to 2 hrs per night will be less able to regulate their appetite, and will therefore eat more food, particularly at night, will eat for reasons other than hunger more often, will rate treat foods as more appealing, and will engage in more sedentary behaviour.

## Methods

The DREAM study is a randomized cross-over trial testing how sleep deprivation influences eating behaviour and activity patterns in children. We will manipulate the overnight sleep duration of healthy school-aged children aged 8–12 years who exhibit no sleep disturbances, in order to assess whether a mild level of sleep deprivation that is common in children affects what, when and how they eat. Using actigraphy across the full 24-h day to measure sleep, sedentary behaviour, and time spent in light, moderate and vigorous activity [43, 49], combined with wearable cameras to provide a passive, but highly informative way of “seeing” first-hand how children spend their time [35, 36], will provide novel data to determine whether sleep deprivation influences patterns of activity and eating behaviours. All children will undergo two experimental sleep conditions, sleep restriction and sleep extension.

### Study design and setting

The DREAM study involves a five-week protocol including a baseline week to establish usual sleep patterns, followed by 1 week of sleep extension and 1 week of sleep restriction, with 1 week of no intervention in between. This design is illustrated in Fig. 1 and detailed in text. The study takes place in Dunedin, New Zealand.

**Fig. 1 Fig1:**
[figure not shown]
Study design

Benefits of the cross-over design include a reduction in the influence of confounders as each child acts as their own control. The week between weeks 3 and 5 with no intervention should eliminate any carry-over effects from one condition to the other [53]. Period effects (that their first visit is different to their second, regardless of condition due to learning effects, or comfort levels at the study, etc.) will be accounted for by randomising to order and including this in the model. The difference between these two conditions should produce a reduction in “usual” sleep time of 1–2 h per night for each child, considered to be a level of mild sleep deprivation common in children [54]. Others report high compliance (95% retention) with similar protocols in children [55, 56],

We have chosen to use a combination of sleep restriction and extension (1 hour each for seven consecutive nights) rather than comparing 2 h of restriction against usual sleep (e.g. baseline against a week of restriction) as pilot work indicated this was more feasible and practical for families. As this is a cross-over trial and children are only compared with themselves, controlling for season is not necessary; however, to remove the potential modifying effect of school holidays, all data collection will be conducted during the school term. In this way, changing bed time while maintaining wake time reflects the real world where wake times remain relatively constant in children [57]. Participants will also undergo two 24-h diet recall sessions during each experimental week. As participants will commence the study on different days of the week, all days of the week will be represented. Wearable cameras will aid researchers in validating the diet recalls. At the end of each experimental week, participants will visit the clinic for a feeding study to assess eating in the absence of hunger. Finally, families will be invited to attend a qualitative exit interview after the study ends, by a researcher with mixed methods experience that has had no previous contact with the participant or caregiver. This qualitative interview will be open-ended and serve as an explanatory tool to compliment the study. All interviews will be audio recorded and professionally transcribed, and analysed thematically. Tables 1 and 2 describe DREAM study events and event locations.

**Table 1 Tab1:** Timing of DREAM activities and study periods

Study activities	Study period			
	*Week 0*	*Week 1*	*Week 3*	*Week 5*
Eligibility screen (SDSC) [58]	X			
Informed consent		X		
Group allocation		X		
Interventions				
Sleep restriction/sleep extension			X	X
Sleep extension/sleep restriction			X	X
Outcome assessments:				
Child				
Actigraphy		X	X	X
Height		X		
Weight		X	X	X
EAH (Feeding experiment)			X	X
*Questionnaires:*				
Food cravings			X	X
Kidscreen [61]			X	X
PROMIS sleep disturbance [62]			X	X
PROMIS sleep impairment [62]			X	X
*Wearable camera			X	X
Primary caregiver				
*Questionnaires:*				
Demographics		X		
Child food allergy and preferences		X		
Child Sleep Hygiene [63]		X		
PROMIS sleep disturbance proxy [62]			X	X
PROMIS sleep impairment proxy [62]			X	X
Child eating behavior (CEBQ) [64]			X	X
Screen time			X	X
Snacks/meals			X	X
Child/caregiver dyad				
*Diet recall (in person) [65]			X	X

* = these measures are used twice in Weeks 3 and 5

**Table 2 Tab2:** Location and description of DREAM study appointments

Study appointment number and descriptor	Location	Purpose of appointment
Appointment 1 – Baseline	Participant’s home	Collection of baseline data
Appointment 2 – DREAM week 1	Participant’s home	Set up for first experimental week
Appointment 3 – Diet recall	Participant’s home	1st diet recall; photo review
Appointment 4 – Feeding experiment 1	Metabolic kitchen (clinic)	2nd diet recall; feeding experiment; photo review
Appointment 5 – DREAM week 2	Participant’s home	Set up for second experimental week
Appointment 6 – Diet recall	Participant’s home	3rd diet recall; photo review
Appointment 7 – Feeding experiment 2	Metabolic kitchen (clinic)	4th diet recall; feeding experiment; photo review
Appointment 8 – Follow up interview	Participant’s home	Qualitative interview

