### Baseline and randomisation

Eligible participants will be seen at a 45–60 min baseline appointment in their home (week 1, Table 1). Primary caregivers will provide written consent for minors at this time, as well as complete online questionnaires assessing demographics (child date of birth, date of survey, household address to calculate household deprivation, ethnicity, family structure), child food preferences and allergies (to plan for the feeding experiment in weeks 3 and 5), and the Children’s Sleep Hygiene Survey [63]. Consent will also be gained from each child participant. Height (Wedderburn Portable Height Rod, WS-HRP) and weight (Tanita electronic scales HD351) will be measured following standard procedures, and an actigraph (the ActiGraph wGT3X-BT) will be provided to be worn on the child’s right hip 24-h a day for 1 week to measure usual sleep, physical activity and sedentary behaviour, initialized with 15 s epochs.

Families will be provided with a Participant Instruction Booklet containing all study instructions. After the baseline appointment is complete, participants will be randomised to start with either sleep restriction or sleep extension during intervention weeks 3 and 5. Randomisation will be stratified by age (grouped by 8–10 and 11–12 years) and gender. Randomisation to order will be generated using random block lengths (Stata 15.1, StataCorp, Texas) and uploaded into the REDCap randomisation module [67].

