#### Power calculations and statistical analyses

Recruiting 110 children will allow for a representative sample, with 20% drop-out and incomplete data. For the objective experiment for our main outcome (eating in the absence of hunger at the feeding experiment), based on a standard deviation of 870 kJ and a within-person correlation of 0.7 [97], a sample size of 59 would be required to detect a difference of 250 kJ in energy intake between the two different sleep conditions (80% power, p < 0.05). Fifty-five children would be required to detect a difference in the eating in the absence of hunger subscales [98] of 0.3 standard deviation. These numbers will also allow us to detect important differences in energy intake (secondary outcome) from the diet recalls, over the total day (500 kJ difference, n = 85) or just at night (200 kJ difference, n = 50) [56]. Mixed effects regression models will be used to determine mean differences between the two conditions with participant identification number as a random effect which accounts for both within-person and between-person variation. Skewed data will be log-transformed as appropriate.

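### Randomised order is a between-child term, so including it in the model does not adjust for the period effects it is meant to handle

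*Protocol article*

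**What the plan says.** The protocol article, Study design and setting (text after Fig. 1), describes a period effect as one in which participants show "that their first visit is different to their second, regardless of condition due to learning effects, or comfort levels at the study". It says that these effects "will be accounted for by randomising to order and including this in the model".

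Baseline and randomisation fixes what order means: "participants will be randomised to start with either sleep restriction or sleep extension during intervention weeks 3 and 5". The sequence is generated in random blocks, stratified by age group and gender.

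Power calculations and statistical analyses describes the model in one sentence: "Mixed effects regression models will be used to determine mean differences between the two conditions with participant identification number as a random effect". It names neither order nor period. The primary sample size is "based on a standard deviation of 870 kJ and a within-person correlation of 0.7"; on these inputs "a sample size of 59 would be required to detect a difference of 250 kJ in energy intake between the two different sleep conditions", at 80% power and p < 0.05. The plan recruits 110 and allows 20% for drop-out and incomplete data.

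**The concern.** The article identifies a specific problem, first visit versus second visit, and names a specific remedy. The remedy does not act on the problem. Which condition came first is a label that a child carries through both visits. It can explain differences between children, but the condition effect in a two-period crossover comes from differences within children. The term that separates a visit effect from a condition effect is the visit itself.

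An analyst who followed the sentence literally would report a period-adjusted result that is not period-adjusted. Any visit effect on snack intake would stay in the residual variance. It would also enter the estimate to the extent that the two orders differ in number after losses and after the exclusion of children who do not report fullness of 4 or 5.

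**Working it through.** **Inputs.** From Power calculations and statistical analyses: SD 870 kJ, within-person correlation 0.7, difference 250 kJ, 80% power, p < 0.05 (taken as two-sided), 110 recruited with 20% loss, so 110 × 0.8 = 88 analysable. Assumed: 1:1 allocation (no ratio is stated) and a period effect P from 0 to 500 kJ (none is given).

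**1. The plan's own figure.** SD of the paired difference = 870 × √(2 × (1 − 0.7)) = 673.9 kJ. The normal approximation gives (673.9 × (1.960 + 0.842) / 250)² = 57.03, rounded up to 58. The exact noncentral t gives power 0.793 at 58 and 0.800 at 59. The stated 59 reproduces.

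**2. What a period effect does.** Let n1 children have extension first and n2 restriction first, with N = n1 + n2. The restriction-minus-extension difference has mean Δ + P in the first group and Δ − P in the second. Without a period term:

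- shift in the estimate = P(n1 − n2)/N
- SE² = (673.9² + 4P²·n1·n2/N²)/N, where the added term equals P² at n1 = n2

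With a period term the shift is 0 and SE = 673.9 × √(1/n1 + 1/n2)/2.

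**3. Does order help?** Random-intercept models were fitted to simulated complete pairs (true effect 250 kJ). Cells show the estimate (SE) in kJ:

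| Split, P | Condition only | + order | + period |
|---|---|---|---|
| 44:44, 500 | 255.6 (96.4) | 255.6 (96.4) | 255.6 (76.1) |
| 48:40, 500 | 315.0 (89.2) | 315.0 (89.2) | 271.6 (73.9) |
| 44:36, 300 | 250.32 (72.45) | 250.32 (72.45) | 228.44 (68.97) |

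Order changes nothing and period does. In the balanced row only the SE moves. Each row is a single simulated dataset, so the estimates also carry sampling error.

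**4. Size, balanced orders, target 250 kJ.** SD of the difference = √(673.9² + P²), with power from the noncentral t:

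| P (kJ) | SD (kJ) | Power, n = 59 | Power, N = 88 | SE, N = 88 (kJ) |
|---|---|---|---|---|
| 0 | 673.9 | 80% | 93% | 71.8 |
| 100 | 681.3 | 79% | 93% | 72.6 |
| 200 | 703.0 | 77% | 91% | 74.9 |
| 300 | 737.7 | 73% | 88% | 78.6 |
| 400 | 783.7 | 67% | 84% | 83.5 |
| 500 | 839.1 | 61% | 79% | 89.5 |

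The n needed for 80% power rises from 59 to 61, 65, 71 and 80 for P = 100 to 400. These powers treat the ±P shift as ordinary noise, which is somewhat pessimistic when the orders are exactly equal, because the estimate itself still varies with SE 71.8. At P = 500 and N = 88 the critical difference is about 1.988 × 89.5 = 177.9. Then (250 − 177.9)/71.8 = 1.00, which gives about 84% rather than 79%.

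**5. Size, unequal orders.** At 48:40 the shift is P × 8/88, that is 9, 23 and 45 kJ for P = 100, 250 and 500. At 44:36 with P = 300 it is 300 × 8/80 = 30 kJ, or 12% of the 250 kJ target, with SE 82 against 76 when period is fitted.

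**The case against.** The wording can be read more kindly. The subject of the sentence is period effects, so the thing included in the model might be visit order, that is, period. This is possible but strained, because order is named immediately before and the randomisation section uses the word for the starting condition. If period was meant, the sentence still needs correcting.

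The one-sentence model description proves little. It omits order as well, so it is not a full list of terms, and a journal article may leave such detail to an analysis plan that is not shown. That stands: the point rests on the sentence in Study design and setting, not on the later silence.

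A reader might infer that the primary estimate is biased. The documents do not support that. Randomisation makes the estimate unbiased on average, the shift is zero with equal orders, and stratified blocks limit imbalance at allocation. Nothing in the article suggests that losses differ by order. Exact equality after losses is unlikely, but only the size of the gap matters.

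A reader might also infer that the stated power is lost. At 88 children it is not, short of a period effect near 500 kJ, twice the target difference. With balanced orders the enlarged SE makes the test conservative, so it does not create false positives.

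Finally, the exact invariance holds for complete pairs. If a mixed model keeps some children with one usable visit, order can alter the result slightly, but it still does not adjust for period.

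**Conclusion.** The stated adjustment does not do what the article says it does. What remains unadjusted is a larger standard error, plus a shift in the estimate proportional to the imbalance between orders. At the planned 88 and an assumed 300 kJ period effect, the SE is 78.6 instead of 71.8 kJ and power is 88% instead of 93%. The shift is zero if the orders are equal and 300 × 8/88 = 27 kJ at 48:40. All of this depends on period-effect sizes that the article does not supply; it names only possible causes.

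Severity is moderate. The margin on the primary outcome is comfortable if 88 children are analysed. It is thinner if the fullness exclusion bites: in the pilot of 11, two children were excluded for fullness and one had incomplete data (3/11 = 27% if these were different children). It is also thin for total-day energy intake, which needs 85 of the 88.

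**What to change.** In Study design and setting, replace the inclusion of order with a fixed effect for period (first or second experimental week). In Power calculations and statistical analyses, state the model as condition and period fixed effects with a participant random effect, for each outcome compared between the two weeks. Order may be added as a sequence check, but it should not be described as the adjustment for period.

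The cost is one degree of freedom and no new data. If there is no period effect the price is negligible: at 48:40 the SE is 72.1 instead of 71.8 kJ.
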